## Abstract

**Background:**

The COVID-19 pandemic and associated social distancing regulations have led to an increased risk of social isolation and physical inactivity, particularly among older adults. The benefits of physical activity for reducing fall risk and improving mood and mental functioning have been well documented. The aim of this trial is to investigate the effect of the *MovingTogether* programme on psychological distress (primary outcome) and physical activity, social capital, cognition, concern about falling, loneliness, physical functioning, quality of life and physical activity enjoyment (secondary outcomes).

**Methods:**

A randomised controlled trial with a waitlist control will be conducted, recruiting 80 adults aged 60+ years with access to Facebook and a computer or tablet and not currently meeting the aerobic physical activity guidelines. Randomisation will be completed using REDCap. The intervention group (*n* = 40) will join a private Facebook group where allied health facilitators will provide targeted healthy lifestyle education throughout the 10-week programme with weekly telehealth group calls. Intervention participants will also be provided access to tailored strength and aerobic exercise guidance and an evidence-based eHealth balance exercise programme. Psychological distress and secondary outcomes will be assessed at baseline, 11 weeks (post-intervention) and 16 weeks (1-month follow-up). Linear mixed models will be applied for each outcome measure as per an intention-to-treat approach to determine the between-group differences. Secondary analyses are planned in people with greater adherence and those with higher psychological distress.

**Discussion:**

COVID-19 has highlighted the need for scalable, effective and novel methods to improve and protect the health of older adults. The integration of an evidence-based fall prevention programme with a mental health-informed online health promotion programme may help to improve mental and physical health outcomes among older adults.

**Trial registration:**

Australian New Zealand Clinical Trials Registry (ANZCTR) ACTRN12621001322820p. Registered on 29 September 2021

**Supplementary Information:**

The online version contains supplementary material available at 10.1186/s13063-022-06978-3.

## Administrative information

Note: The numbers in curly brackets in this protocol refer to the SPIRIT checklist item numbers. The order of the items has been modified to group similar items (see http://www.equator-network.org/reporting-guidelines/spirit-2013-statement-defining-standard-protocol-items-for-clinical-trials/).

## Introduction

### Background and rationale {6a}

Older adults, classified as people aged 60+ years [1], are at an increased risk of experiencing health issues such as mental health problems and falls [2]. Psychological distress increases one’s risk of falling due to the demanding use of the working memory that is also needed for activities requiring complex attention and coordination [3]. Similarly, experiencing depressive symptoms is a risk factor for falling in older adults, independent of other factors like antidepressant use and reduced executive and physical functioning [4]. Given the bi-directional relationship between falls and mental health, interventions aiming to reduce fall risk may simultaneously improve mental health outcomes, and vice versa [5].

Falls are the leading cause of morbidity and mortality among older adults and can lead to ongoing physical disability, fear of falling, social isolation and loneliness [6, 7]. There is strong evidence that specific exercise that includes a challenge to balance is effective in reducing the rate of falls among older people living in the community [8]. Achieving physical activity guidelines of 150 min of moderate to vigorous activity [9] has been recommended to manage mental health conditions and is protective against incident depression in adults aged > 60 years [10]. Additionally, physical activity is protective against osteoporosis, all-cause and cardiovascular mortality, certain cancers, disability, functional limitation, cognitive decline and dementia [11].

Due to the COVID-19 pandemic, there has been a decline in social connection [2] as well as physical activity among older adults [12]. Older adults are more likely to be self-isolating than the general population, often for extended durations due to comorbidities and government recommendations [13], therefore increasing the risk of psychosocial issues for older adults. Loneliness is a risk factor for depressive symptoms in those aged over 50 [14], and decreased social connection is another modifiable risk factor for older adults being more vulnerable to loneliness, poor mental health and decreased quality of life [2]. Subsequently, older adults face an increased risk of depression, anxiety and stress-related disorders in response to the pandemic [15].

Isolation in older people is not only limited to pandemics and can occur when people are limited by disease comorbidities or even the weather. It is therefore important to find better mechanisms to address reduced physical activity levels and social connectedness for older adults during extended periods of isolation. *StandingTall* is an evidence-based, eHealth fall prevention programme that includes a progressive balance and strength training programme plus health education that has demonstrated efficacy for the rate of falls over 2 years [16, 17]. Adherence to the recommended dose of 2 h per week was high throughout the study period, with limited attrition, but there was no effect on psychological well-being [17]. A qualitative study further highlighted that while participants valued being able to do the exercises in their own time at home, many participants also highlighted the lack of social connections as a limitation of the programme [18]. We hypothesise that the addition of specific strategies that target mental health, through a social media platform, will address this limitation and improve its effectiveness for mental health.

We recently conducted a pilot study that evaluated a health promotion programme delivered via a private Facebook group to eleven socially isolated older adults during the COVID-19 pandemic in 2020 [19]. The programme was adapted from a Facebook-delivered, mental health-informed physical activity programme that was effective at reducing psychological distress in emergency service workers and their support partners [20, 21]. Similarly to emergency service workers and those in their support system, older adults are at risk of poor mental health, so the programme was then modified to have targeted content for older adults. The pilot study illustrated feasibility, high acceptability and preliminary effectiveness for secondary outcomes including psychological distress and quality of life [19].

### Objectives {7}

This randomised controlled trial (RCT) will enhance the design of the programme used in the pilot study by adding *StandingTall*, creating the *MovingTogether* programme. It is hypothesised that *MovingTogether* will improve both mental health outcomes, primarily psychological distress and physical health outcomes.

### Trial design {8}

A two-arm, superiority RCT will be conducted with participants randomly assigned (1:1) to either the intervention group (*n* = 40) or the wait list control group (*n* = 40). The design of this protocol was guided by the Standard Protocol Items: Recommendations for Interventional Trials (SPIRIT) checklist [22] and the Template for Intervention Description and Replication (TIDieR) checklist (Table 1) [29]. Reporting of the results from this trial will be guided by the Consolidated Standards of Reporting Trials (CONSORT) checklist [30].

**Table 1 Tab1:** Template for Intervention Description and Replication (TIDier) checklist for the *MovingTogether* trial protocol

Item number	Item	Description
1	Brief name	An online health promotion, physical activity and social support, *MovingTogether* programme for older adults.
2	Why	Due to the COVID-19 pandemic, there has been a decline in social connection and physical activity in older adults, a population that is already at an increased risk of experiencing health issues such as mental health problems and falls. Given the bi-directional relationship between falls and mental health, interventions aiming to reduce fall risk may simultaneously improve mental health outcomes, and vice-versa. Physical activity is one strategy that can improve mental health and decrease fall risk, and using technology for service delivery is an emerging area of research for mental healthcare.
3	What materials	• Weekly educational written and video posts delivered in the *MovingTogether* private Facebook group (see Table 2). • *StandingTall* eHealth fall prevention programme. • Participants may use a folded towel (substituted for a foam cushion) for *StandingTall* exercises. • Tailored aerobic and strength exercise programmes including pictures and written descriptions. • Participants who choose to join weekly group telehealth calls will use Zoom, a freely available live call application. • Facebook is a freely available social media platform that participants and facilitators will use to communicate.
4	What procedures	When participants gain access to the 10-week programme, they will join a private Facebook group. The group will be used for social support and communication and to deliver healthy lifestyle education to participants. The facilitators will tailor aerobic and strength exercise programmes for each individual and instruct participants on the use of *StandingTall* balance exercises. Optional weekly group video calls will also be available.
5	Who provided	The facilitators are members of the research team who are allied health professionals (Accredited Exercise Physiologists and an Accredited Practising Dietitian). Allied health facilitators will have experience working with people with mental health conditions and/or older adults. At least one member of the facilitating team will be required to have their mental health first aid accreditation.
6	How	There are both group and individual activities in the programme that will be completed online.
7	Where	The trial will be completed online, using social media (Facebook), video calls (Zoom) and an eHealth fall prevention programme (*StandingTall*).
8	When and how much	Over the 10-week programme, the duration and frequency that individuals complete their *StandingTall* exercises and aerobic and strength training will vary depending on individual circumstances and goals. However, the facilitators will guide most participants to reach 2 h per week of *StandingTall* exercises, at least 150 min of moderate to vigorous intensity aerobic exercise and two sessions of muscle strengthening per week.
9	Tailoring	Accredited Exercise Physiologists will design tailored exercise programmes for all individuals depending on their health conditions, functional ability, interests and goals. Similarly, the *StandingTall* website regularly re-evaluates each individual’s balance performance and adjusts the intensity and level of challenge accordingly.
10	Modifications	Not applicable as the trial intervention has not been delivered yet.
11	Planned intervention adherence assessment	Facilitators will be recording how many participants view each educational Facebook post. Adherence to *StandingTall* training and individual aerobic and strength programmes will also be monitored. Participants will be contacted privately by study investigators if they choose not to attend calls for at least two consecutive weeks and/or if they do not reach their recommended exercise dose for two consecutive weeks.
12	Actual intervention delivery	Not applicable as the trial intervention has not been delivered yet.

## Methods: participants, interventions and outcomes

### Study setting {9}

All participants will be living in Australia, although the trial will be completed entirely online.

### Eligibility criteria {10}

Individuals will be considered eligible if they meet the following inclusion criteria: (i) aged 60+ years; (ii) proficient in written and spoken English; (iii) living independently in the community, in Australia; (iv) able to mobilise indoors without the use of a walking aid; (v) have access to the Internet at home, Facebook and either computer, laptop or iPad/tablet access; and (vi) self-reported to be currently participating in less than 150 min of moderate to vigorous intensity physical activity per week through the use of the Physical Activity Vital Sign Questionnaire [31].

Individuals will be excluded from the study if (i) they have high levels of psychological distress (score of > 30 on the K10) unless deemed to have support from a mental health professional or (ii) they have a high risk of suicidal behaviour (score of > 21 on the SIDAS) unless deemed eligible to participate by a clinical psychologist through a suicide risk assessment. Other exclusion criteria are (i) absolute contraindications to exercise according to the American College of Sports Medicine (ACSM) or relative contraindications without medical clearance to exercise [32], (ii) currently participating in a fall prevention programme at least weekly, (iii) signs of cognitive impairment (score < 4) as assessed by the Ottawa 3DY or (iv) diagnosis of a progressive neurological condition.

### Who will take informed consent? {26a}

If participants confirm they would like to be involved after reading the participant information statement and consent form, they will be emailed a link to provide online consent and to complete screening questionnaires via Research Electronic Data Capture (REDCap). REDCap is a secure web platform that will be used by facilitators to collect data throughout the trial [33]. Alternatively, upon request, participants may be screened and complete future trial questionnaires via a phone call with the primary study investigator, initiated by verbal consent.

### Additional consent provisions for collection and use of participant data and biological specimens {26b}

Not applicable, no samples were collected.

### Interventions

#### Explanation for the choice of comparators {6b}

A waitlist control design allows all participants to eventually have access to the programme.

#### Intervention description {11a}

The *MovingTogether* intervention has three essential components, i.e. a Facebook-delivered healthy lifestyle education and support programme, an eHealth fall prevention programme (*StandingTall*) and an aerobic and strength exercise programme tailored to each participant.

Participants will be asked to join the *MovingTogether* private Facebook group. Facilitators will monitor the group at least once every weekday over the 10-week period. Targeted education and resources will be provided to participants through the online Facebook group, and facilitators will encourage discussion between all members of the group, regarding a variety of lifestyle topics. Topics will include behaviour change, overcoming barriers, reducing sedentary behaviour, increasing physical activity, increasing structured exercise, balance training and healthy eating (see Table 2). Education on a single topic will be the focus of a single week (2 weeks in the case of the nutrition topic), and new material will be released every week. These educational materials have been designed specifically for this study by the facilitators who are allied health professionals (Accredited Exercise Physiologists and an Accredited Practising Dietitian) and will be delivered as written resources or videos. Allied health facilitators will have experience working with people with mental health conditions and/or older adults. At least one member of the facilitating team will be required to have their Mental Health First Aid Accreditation. Participants will be encouraged to discuss shared experiences with participation in the programme and more general life experiences and to support each other. Additionally, participants can choose to join an optional weekly 20–30-min group video call [19], to further promote the social connection between participants and to follow up and create discussion about the provided educational materials. Facilitators will run calls twice weekly to allow multiple time options to join.

**Table 2 Tab2:** *MovingTogether* weekly intervention content

Week	Topics	Content
1	Introductions, safety and *StandingTall*	○ Participants invited to introduce themselves ○ Participants directed to the *Safe Exercise at Home* safety checklist [23] ○ Group set up of *StandingTall* and individual baseline assessment led by AEP through a live video call
2	Starting *StandingTall*	○ Prompted to start using the *StandingTall* programme
3	Exercise education	○ Education on aerobic, resistance and balance training and how often to complete these based on the physical activity guidelines [9]
4	Behaviour change	○ Goal setting education and participants to create personal goals in a style that suits the individuals [24] ○ Forming and tracking habits ○ Invited to talk to AEP about progressing *StandingTall* use
5	Nutrition	○ Live video call with an Accredited Practising Dietitian including: - Fuelling the body with good nutrition [25, 26] - Creating a healthy food environment, for example, mindfully eating meals - Nutrition for mental health, brain health and fall prevention ○ Individual diet investigation through the University of Newcastle’s Healthy Eating Quiz [27, 28]
6	Nutrition	○ Live question and answer session with an Accredited Practising Dietitian
7	Barriers and follow-up on behaviour change	○ Facebook poll used to reflect the specific barriers to exercise and barriers to healthy eating faced by the individuals in the group ○ Suggested strategies to address barriers ○ Follow-up on goal setting ○ Invited to talk to AEP about progressing *StandingTall* use
8	Starting aerobic and resistance exercise	○ Participants encouraged to determine what level of exercise is suited to them based on the provided *Safe Exercise at Home* guide [23] ○ Exercise ideas shared for all different levels through documents and real-time videos ○ Individuals invited to privately speak to an AEP about a tailored aerobic and strength exercise programme
9	Reducing sedentary behaviour	○ The risks of sedentary behaviour and the importance of breaking up sitting time ○ Suggested ways to break up sitting time
10	Review	○ Individualised approach to maintaining aerobic, strength and *StandingTall* exercise ○ Recommendations to online and community programmes ○ How to access a private exercise physiologist ○ Review of goals ○ Celebration of progress

The *StandingTall* eHealth programme provides home-based exercise to improve balance and reduce fall risk [16]. Individuals will be provided with access to the programme and a manual on setting up and using the application. They will join a small group video call to receive assistance from a facilitator to set up the app and will be encouraged to contact the primary study investigator for assistance with any technological difficulties or queries. The app will provide participants with an individualised exercise programme that will suit their abilities, but remains challenging, based on a baseline balance assessment. This assessment will be completed in week 1 when the participants are guided to set up their *StandingTall* account. The programme will be progressed automatically based on the reported rate of perceived exertion through training. Exercises will train static and dynamic balance, stepping in different directions, functional strength and dual-task activities. Frequency, duration, intensity and dose of *StandingTall* training will be individualised to participants, but participants will be guided by facilitators to set goals around completing their exercise programmes with the aim of encouraging all to gradually complete a recommended dose of 2 h of balance training per week. Website analytics will track adherence data and time spent on the app data through individual logins.

Participants will also receive individualised support from allied health facilitators, including tailored aerobic and strength exercise programmes prescribed by Accredited Exercise Physiologists depending on participants’ health needs and activity interests. Exercise programmes will be designed to encourage participants to reach the physical activity guidelines of 150 min of moderate to vigorous activity, unless the participant indicates during goal setting that this volume is unrealistic for their abilities and/or circumstance [9].

At the conclusion of the 10-week programme, the Facebook groups and *StandingTall* programme will remain accessible without input from facilitators. The waitlist control group will also have access after their final assessment at 14 weeks from baseline. They will join a private Facebook group (separate from the intervention group) and complete the facilitated intervention without answering additional questionnaires. Based on feedback from the intervention group, the researchers will be using the waitlist control programme to trial new features of the programme such as additional topics suggested.

#### Criteria for discontinuing or modifying allocated interventions {11b}

Participants who experience any change to their health during the trial that precludes exercise will still be permitted to receive the non-exercise-related components of the intervention; however, their data will be excluded from the analysis, as exercise is a key component of the intervention.

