#### Strategies to improve adherence to interventions {11c}

Participants will be contacted privately by study investigators if they choose not to attend calls for at least two consecutive weeks and/or if they do not reach their recommended exercise dose for two consecutive weeks. This is to ensure they receive support to reach their goals and to promote adherence to the exercise components of the programme.

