#### Assignment of interventions: allocation

##### Sequence generation {16a}

Randomisation will use randomly permuted block sizes of 2, 4 and 6 within an online REDCap database. Participants will be allocated (1:1) to either the intervention or waitlist control group after they have been screened for eligibility, provided consent and completed all baseline measures. Participants in the same household will be considered one unit for this process.

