## Statistical methods

### Statistical methods for primary and secondary outcomes {20a}

Data analysis using IBM SPSS 25 will evaluate whether there are any significant changes between baseline and post-intervention on psychological distress and secondary outcomes, as well as between baseline and results at the follow-up point. Linear mixed models will be applied for each outcome measure, excluding physical activity, conducted using the MIXED procedure (considering data at all time points). A generalised linear mixed model with appropriate distribution will be used to analyse physical activity, measured by the IPEQ. Time will be considered a categorical variable for each outcome. Effect sizes (Cohen’s *d* and the 95% confidence intervals) will be calculated to determine the size of the within-group change between before and after treatment and between before treatment and 1-month post-intervention. Time, group and the interaction between these will be used as predictors. Marginal means drawn from the mixed models will be used.

Analyses will use all available data as per an intention-to-treat approach. The between-group difference at post-intervention and follow-up from baseline [mean difference (MD) and 95% confidence interval] will be calculated for all outcome measures using a baseline-adjusted mixed model with group as the independent variable, post-programme (week 10) and also follow-up (week 14) score on the outcome measures as the dependent variables, baseline score on the outcome measure as a covariate, and statistical significance set at *P* < 0.05. The results and effects will be reported as unadjusted and adjusted for sex and age. Time, group and the interaction between these will be used as predictors.

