### Methods in analysis to handle protocol non-adherence and any statistical methods to handle missing data {20c}

A sub-group analysis is planned to include participants who complied with the intervention, including those who reached a *StandingTall* training duration of at least 2 h per week. We will report the number of participants with missing scores for each outcome.

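### Excluding randomised participants who become unable to exercise contradicts the stated intention-to-treat analysis and can bias the K10 comparison, probably but not certainly towards the intervention

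*Protocol article*

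**What the plan says.** In the Protocol article, Criteria for discontinuing or modifying allocated interventions {11b} covers anyone whose health alters mid-trial in a way that rules out exercise. Such a person may go on receiving the parts of the programme that involve no exercise, but "their data will be excluded from the analysis, as exercise is a key component of the intervention".

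Statistical methods for primary and secondary outcomes {20a} states: "Analyses will use all available data as per an intention-to-treat approach". The Methods part of the abstract agrees: "Linear mixed models will be applied for each outcome measure as per an intention-to-treat approach to determine the between-group differences".

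Non-adherence has a separate place in the plan. Section {20c} says "A sub-group analysis is planned to include participants who complied with the intervention", and section {20b} lists the same group among the subgroup analyses of psychological distress.

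Under Sequence generation {16a}, allocation takes place "after they have been screened for eligibility, provided consent and completed all baseline measures". Under Strategies to improve adherence {11c}, investigators contact participants "if they do not reach their recommended exercise dose for two consecutive weeks". The Intervention description {11a} adds that app logins track training time, and that waitlist participants receive the programme only after their final assessment at 14 weeks.

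**The concern.** The two rules for who is analysed are incompatible. A participant who can no longer exercise may stay in the programme and may have K10 scores on file. One section discards those scores and another uses them. Nothing in {11b} limits the exclusion to a secondary analysis, and the complier analysis in {20b} and {20c} already does what its stated reason calls for. As written, it is a per-protocol rule applied to the main analysis.

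Randomisation protects the comparison only if everyone randomised is kept. The trigger here is a post-randomisation health change, which an exercise programme can itself cause, for example through injury. It is also likely to be related to the outcome, since the Background links falls, disability, isolation and poor mental health. If such people are removed more often from one arm than the other, the difference in mean K10 shifts for reasons unrelated to the programme's effect. Blinding the analysts does not prevent this, because the selection depends on what happens to participants and not on how the data are modelled.

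**Working it through.** **Inputs from the protocol.** K10 runs from 10 to 50, and higher is worse. Sample size {14} gives SD 6.41, correlation 0.6, 68 evaluable, 15% dropout and 80 in total, allocated 1:1. Significance is at P < 0.05, taken here as two-sided.

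**The plan's own figure.** 68 / (1 − 0.15) = 80, which reproduces the stated total. The base of 68 cannot be checked because the moderate effect has no number, but nothing below depends on that effect.

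**Inputs that are assumptions.** The documents do not give the share excluded in the intervention arm (f_I) or in the control arm (f_C). Nor do they say by how much the excluded participants' K10 is worse than that of those remaining in the same arm (g).

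**Shift in the between-group difference.** Dropping a share f whose mean is g points higher lowers that arm's mean by f × g. The net shift towards the intervention is (f_I − f_C) × g.

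**False-positive rate with no true effect.** Take 34 per arm before exclusion, so n_I = 34 × (1 − f_I) and n_C = 34. Then SE = 6.41 × k × √(1/n_I + 1/n_C), with k = 1 for an unadjusted comparison and k = √(1 − 0.6²) = 0.8 with baseline adjustment. With b = shift / SE, the two-sided rate is P(Z > 1.96 − b) + P(Z < −1.96 − b).

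Worked case, f_I = 10%, f_C = 0, g = 6.41, baseline-adjusted:
- n_I = 30.6
- SE = 6.41 × 0.8 × √(1/30.6 + 1/34) = 1.28
- shift = 0.10 × 6.41 = 0.64
- b = 0.64 / 1.28 = 0.50
- rate = 7.9%

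Exclusions in the intervention arm only:

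| Excluded | g (points) | Shift (points) | Shift (SD) | Rate, unadjusted | Rate, adjusted |
|---|---|---|---|---|---|
| 5% | 3.2 (0.5 SD) | 0.16 | 0.025 | 5.1% | 5.2% |
| 5% | 6.41 (1 SD) | 0.32 | 0.05 | 5.5% | 5.7% |
| 10% | 3.2 (0.5 SD) | 0.32 | 0.05 | 5.5% | 5.7% |
| 10% | 6.41 (1 SD) | 0.64 | 0.10 | 6.9% | 7.9% |

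Exclusions in both arms, g = 6.41:

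| f_I | f_C | Shift |
|---|---|---|
| 10% | 5% | 0.32 towards the intervention |
| 10% | 10% | 0 |
| 5% | 10% | 0.32 towards control |

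The sign therefore depends on which arm loses more people, and the size on how unwell they are. The contradiction between {11b} and {20a} depends on neither.

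**The case against.** The contradiction itself has no good answer in the text. The strongest objection is to claiming more than the contradiction.

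- **Direction.** A reader might infer that the rule simply biases the trial towards the intervention because equally unwell controls stay in. The documents do not say so. Section {11b} speaks of participants and is not restricted to one arm. That controls are retained is an inference from the wording about the intervention, from the exercise follow-up in {11a} and {11c}, and from the waitlist's delayed access. The inference is plausible, but equal exclusion gives no bias and the reverse pattern changes the sign. This objection stands, so the direction is stated only as probable.
- **Hidden harm.** A reader might infer that exclusion conceals harm. Adverse events are reported separately under {22} and {23}, whatever the analysis set. At most, worsening on the questionnaires could be masked.
- **Lost power.** A reader might count the exclusions on top of the 15% dropout. Section {14} does not say what the 15% covers. If they are additional, a further 5% or 10% leaves 68 × 0.95 ≈ 65 or 68 × 0.90 ≈ 61, and power falls from 80% to about 78% or 76%.
- **Size.** Every input to the shift is assumed, and at the mild end the effect on the error rate is negligible. That is true. The severity therefore rests on the conflict with intention-to-treat and not on these figures.

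**Conclusion.** The concern holds and must be fixed. The protocol states two incompatible rules for who enters the analysis, and one of them removes randomised participants because of a post-randomisation event that the intervention can cause and that exercise monitoring follows only in the intervention arm before the final assessment. The resulting bias in K10 probably, but not certainly, favours the intervention. On the assumption that only the intervention arm loses 5% to 10%, with K10 worse by 0.5 to 1 SD, it is 0.16 to 0.64 points, with a two-sided false-positive rate of about 5.1% to 8%. Similar exclusions in both arms would leave it near zero, and heavier exclusion among controls would reverse it.

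**What to change.** Reconcile {11b} with {20a}. Delete the exclusion from the primary analysis. State that everyone randomised is analysed in the allocated arm with all K10 data collected, whether or not they could exercise. Scores that were not collected are reported as missing, in line with the reporting already planned in {20c}. If the sponsor wants results without these participants, give them as a labelled sensitivity analysis that applies the same criterion to both arms.

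The cost is about one sentence in the protocol or SAP. Trial status records that data collection was completed on 3 October 2022, so the change concerns only which collected data are analysed. The arrangement for receiving the non-exercise components is not affected.
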